**7.5.1 Temporary treatment discontinuation with investigational product**

Re-initiation of treatment with the Investigational Product will be done under close and appropriate clinical/and or laboratory monitoring once the Investigator has considered according to his/her best medical judgment that the role of the Investigational Product(s) in the occurrence of the event concerned was unlikely and there is no other contraindication to continuing in the study.

All temporary treatment discontinuation (< 10 days) and the date of treatment re-initiation should be recorded by the Investigator on the appropriate CRF pages when considered to be confirmed

**7.5.2 Definition treatment discontinuation with investigational product(s)**

A patient should discontinue the study drug for any of the following reasons:

- Intercurrent condition that requires discontinuation of the study (e.g. lab abnormalities).
- Positive serum pregnancy test or desire to become pregnant
- Contraception cessation

**7.5.3 Handling of patients after definitive treatment discontinuation**

Patients will be followed according to the study procedures as specified in this protocol up to the scheduled date of study completion, or up to recovery or stabilization of an AE, whichever comes last.

All withdrawals should be recorded by the Investigator on the appropriate CRF pages when considered to be confirmed.

All patients who have discontinued the study drug prior to the last visit should have a complete end-of-study visit at three months.

For patients considered lost to follow-up, the CRF must be completed up to the last visit performed. The Investigator should make every effort to contact the patient and to identify the reason why he/she failed to attend the visit and to determine his/her health status.

**8. Safety**

**8.1 Adverse event monitoring**

All events will be managed and reported in compliance with all applicable regulations and will be included in the final Clinical Study Report.

**8.2 Definition of adverse event and serious adverse event**

An Adverse Event is any untoward medical occurrence in a patient or clinical investigation patient administered a pharmaceutical product and which does not necessarily have to have a causal relationship with this treatment. Adverse events include symptoms (nausea, chest pain, et al.), physical signs (tachycardia, hepatomegaly ) or abnormal laboratory examination results.

A Serious Adverse Event is any untoward medical occurrence that at any dose:

 Results in death, or

 Is life-threatening, or

Requires inpatient hospitalization or prolongation of existing hospitalization, or

Results in persistent or significant disability/incapacity, or

 Is a congenital anomaly/birth defect, or

 Is a medically important event

Note: The term "life-threatening" in the definition of "serious" refers to an event in which the patient was at risk of death at the time of the event; it does not refer to an event which hypothetically might have caused death if it were more severe.

Medical and scientific judgment should be exercised in deciding whether expedited reporting is appropriate in other situations, such as important medical events that may not be immediately life-threatening or result in death or hospitalization but may jeopardize the patient or may require intervention to prevent one of the other outcomes listed in the definition above.

A non-serious adverse event (NSAE) is any event that does not fit in the definition of SAE. Again, it is important to collect information on all NSAEs whether or not it is related to the study event.

The intensity of the NSAE was classified as the follows:

1=Mild: Transient or mild discomfort; no medical intervention/therapy required.

2=Moderate: Mild to moderate limitation in activity - some assistance may be needed; no or minimal medical intervention/therapy required.

3=Severe: Marked limitation in activity, some assistance usually required; medical intervention/therapy required, hospitalization possible.

The NSAEs are classified into six grades according to their causal relationship with the treatment.

1. Sure
2. Very probable
3. Probable
4. Possible
5. Doubtful
6. Appears excluded

**8.3 Adverse event recording**

All Adverse Events regardless of seriousness or relationship to Investigational Product, spanning the time from the first visit planned in the Clinical Trial Protocol/signature of the informed consent (i.e., occurring during the washout period) to the last visit planned in the

protocol, the relative treatment are to be recorded on the corresponding page(s) included in the Case Report Form. Whenever possible, symptoms should be grouped as a single syndrome or diagnosis. The Investigator should specify the date of onset, date of cease, intensity, action taken with respect to Investigational Product, corrective treatment/therapy given, outcome and his/her opinion as to whether there is a reasonable possibility that the Adverse Event was caused by the invesigational product.

All adverse events during the study period must be recorded, Efficacy endpoints will not be considered as AEs except if, because of the course or severity or any other features of such events, the Investigator, according to his/her best medical judgment, considers these events as exceptional in this medical condition.

**8.4 Adverse event treatment**

In the case of a Serious Adverse Event the Investigator must immediately:

SEND (within 1 working day, preferably by fax) the signed and dated corresponding page(s) in the Case Report Form to the representative of the Monitoring Team whose name, address and fax number appear on the Clinical Trial Protocol;

ATTACH a photocopy of all examinations carried out and the dates on which these examinations were performed. Care should be taken to ensure that the patient's identity is protected and the patient's identifiers in the Clinical Trial are properly noted on any copy of source documents provided to the Sponsor. For laboratory results, include the laboratory normal ranges;

Follow‐up of any Serious Adverse Event that is fatal or life threatening should be provided within one additional calendar week.

**8.5 Follow-up**

The Investigator should take all appropriate measures to ensure the safety of the patients; notably, he should follow up the outcome of any Adverse Events (clinical signs, laboratory values or other, etc.) until the return to normal or stabilization of the patient's condition;

In the case of any Serious Adverse Event, the patient must be followed up until clinical recovery is complete and laboratory results have returned to normal, or until progression has been stabilized. This may imply that follow‐up will continue after the patient has left the Clinical Trial and that additional investigations may be requested by the Monitoring Team;

In the case of any Serious Adverse Event brought to the attention of the Investigator at any time after cessation of Investigational Product and considered.

**9 Study Procedures**

**9.1 Screening (V0): 4 weeks before randomization**

A screening form will be completed for all patients in whom enrollment is considered. The patient will receive complete information about the study, both orally and in writing. Consent will be obtained directly from the subject prior to enrollment. Baseline evaluation will include patient demographic information, medications, past medical history, family history, cigarette and alcohol use, examination findings. A physical examination will be performed, including measurement of weight (kg), waist and hip circumference, and vital signs (supine systolic and diastolic blood pressure, heart rate). Laboratory tests will be performed (liver and renal function, OGTT blood glucose, HbA1c, HbsAg, HCV-Ab, electrocardiogram and hepatic fat content by 1H MRS).

**9.2 Visit 1 (V1)**

Evaluation before randomization will include patient demographic information, medications, diet and exercise information, past medical history, family history, cigarette and alcohol use, and physical examination. Laboratory tests will be performed (liver and renal function, OGTT blood glucose + insulin, HbA1c, lipid profile, blood and urine routine, urine pregnancy test and hepatic fat content by 1H MRS).

The statistician will develop a master randomization list, with stratification blocked to assure an equal distribution of treatments at each participating site. A study number will correspond to a specific medication packet. This identifying number will be coded on the enrollment confirmation.

The patient will receive 4-week study medication and be instructed how to take the study medication. Time of first study drug administration will be recorded. Study drug will be started the next day after randomization. participants receive standardized recommendations concerning life-style modification (dietary modification, weight loss, exercise).

 An appointment will be made for next study visit (4 weeks after randomization).

**9.3 Visit 2 (V2): 4 weeks after randomization**

Evaluation will include patient concomitant diseases and Concomitant medications, diet and exercise diary. A physical examination will be performed, including measurement of weight (kg) , waist and hip circumference, and vital signs (supine systolic and diastolic blood pressure, heart rate)Laboratory tests will be performed (liver and renal function, OGTT blood glucose + insulin, blood and urine routine).

participants receive standardized recommendations concerning life-style modification (dietary modification, weight loss, exercise).

Compliance will be assessed by counting returned tablets using the equation as the follows:

Compliance=(dispensed drug tablets- returned drug tablets) /planned drug tablets

The compliance should be been 80%-120%.

All adverse events will be managed and reported in compliance with all applicable regulations.

The investigator should dispense the specific drugs determined at randomization to eligible participants at each visit.

An appointment will be made for next study visit (8 weeks after randomization).

**9.4 Visit 3 (V3): 8 weeks after randomization**

Evaluation will include patient concomitant diseases and Concomitant medications, diet and exercise diary. A physical examination will be performed, including measurement of weight (kg) , waist and hip circumference, and vital signs (supine systolic and diastolic blood pressure, heart rate). Laboratory tests will be performed (liver and renal function, OGTT blood glucose + insulin, blood and urine routine).

participants receive standardized recommendations concerning life-style modification (dietary modification, weight loss, exercise).

Compliance will be assessed by counting returned tablets using the equation as the follows:

Compliance=(dispensed drug tablets- returned drug tablets) /planned drug tablets

The compliance should be been 80%-120%.

All adverse events will be managed and reported in compliance with all applicable regulations.

The investigator should dispense the specific drugs determined at randomization to eligible participants at each visit.

An appointment will be made for next study visit (12 weeks after randomization).

**9.5 Visit 4 (V4): 12 weeks after randomization**

Evaluation will include patient concomitant diseases and Concomitant medications, diet and exercise diary. A physical examination will be performed, including measurement of weight (kg) , waist and hip circumference, and vital signs (supine systolic and diastolic blood pressure, heart rate). Laboratory tests will be performed (liver and renal function, OGTT blood glucose + insulin, blood and urine routine).

participants receive standardized recommendations concerning life-style modification (dietary modification, weight loss, exercise).

Compliance will be assessed by counting returned tablets using the equation as the follows:

Compliance=(dispensed drug tablets- returned drug tablets) /planned drug tablets

The compliance should be been 80%-120%.

All adverse events will be managed and reported in compliance with all applicable regulations.

The investigator should dispense the specific drugs determined at randomization to eligible participants at each visit.

An appointment will be made for next study visit (16 weeks after randomization).

**9.6 Visit 5 (V5): 16 weeks after randomization**

Evaluation will include patient concomitant diseases and Concomitant medications, diet and exercise diary. A physical examination will be performed, including measurement of weight (kg) , waist and hip circumference, and vital signs (supine systolic and diastolic blood pressure, heart rate). Laboratory and imaging tests will be performed (liver and renal function, OGTT blood glucose + insulin, HbA1c, blood and urine routine, lipid profile, urine pregancy test, electrocardiogram and hepatic fat content by 1H MRS).

Compliance will be assessed by counting returned tablets using the equation as the follows:

Compliance=(dispensed drug tablets- returned drug tablets) /planned drug tablets

The compliance should be been 80%-120%.

All adverse events will be managed and reported in compliance with all applicable regulations.

An appointment will be made if additional follow up is necessary. Conditions which need additional follow up include adverse event or abnormal laboratory test result.

**10 Statistical Considerations**

**10.1 Statistical Analysis Plans**

This section is an overview of the statistical considerations. Complete details can be found in the Statistical Analysis Plan (SAP). It provides the general specifications for the analysis of the

data to be collected and presented in the Clinical Study Report. A final SAP will be issued prior to database lock and before code breaking. The SAP will define all “pre-specified, planned analyses.”

**10.2 Sample Size Estimation**

The planned sample size for the trial was 180 patients with equal allocation to each of the three treatment groups (60 per group). The sample size estimates were based upon a two-group, binomial comparison of the proportions of patients satisfying the decrease in liver fat content over the course of treatment either with pioglitazone or berberine. Since our current study had three treatment groups and two primary hypotheses, the assumption was made that the two primary comparisons, pioglitazone vs. no-drug control and berberine vs. no-drug control, required the type I error estimate be reduced from 0.05 to 0.016 in accordance with three-group comparison. Expected proportions improved were speculated using pilot data from pioglitazone-treat NAFLD studies. There were no available data at the time of study design to estimate liver steatosis response with berberine, which was assumed, for purposes of planning the trial, to be the same as for pioglitazone.

The sample size calculations were performed using the formula: n1=n2=2[(tα+ t2β)s/δ]^2^ with a standard deviation of NAFLD patients liver fat content (s=6.87%, from our prior study), with an expected difference in proportion of improvement between pioglitazone or berberine group and the control group (δ=0.05), with an α level of two-sided type I error (0.016, corrected for three-group comparison), and with a β level of type II error (0.10; i.e., 90% power). The number per group, using the above assumptions was 52. Inflating this number by the 15% expected missing data rate yielded approximately 60 patients per group, or a total of 180 for the trial.

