**Protocol Synopsis**

| **Title:** | Role of Pioglitazone and Berberine in the Treatment of Non-alcoholic Fatty Liver Disease(NAFLD) Patients With Impaired Glucose Regulation or Type 2 Diabetes Mellitus |
| --- | --- |
| **Primary Objective:** | To assess the effects and safety of pioglitazone (15mg daily), a thiazolidinedione insulin sensitizer, and Berberine (BBR), a component isolated from a Chinese herb, on hepatic fat content and glucose and lipid metabolism in NAFLD patients with impaired glucose regulation (IGR) or T2DM. |
| **Study Design:** | The study is a three-center, randomized, parallel controlled, open clinical trial of treatment with pioglitazone, berberine or no drug on the basis of life style intervention for NAFLD patients with IGR or T2DM. The screening period for evaluating eligibility and collecting baseline data lasted up to 4 weeks before randomization. Eligible patients were randomized to receive pioglitazone (15 mg q.d), berberine (0.5g t.i.d.) or no-drug on basis of Life style intervention for 16 weeks. The primary comparison will be made using an intention-to-treat analysis of the change in OGTT (glucose, insulin, AUC of glucose), HbA1c; lipid profile（TC, TG, HDL-c, LDL-c, ApoA, ApoB, ApoE, Lpa); liver enzymes (ALT, AST, γ-GT, ALP). The secondary outcome is liver fat content by 1H NMR spectroscopy. |
| **Patient Population:** | Patients aged 18 to 65 years with fatty liver (Hepatic fat content assessed by ^1^H MRS were no less than 13%) and impaired glucose metabolism were enrolled. |
| **Inclusion Criteria:** | 1.Patients must have an age range between 18 to 65 years(inclusive).  2. Patients with Liver fat content assessed by 1H MRS≥13%.  3. Patients must meet the criteria for impaired glucose regulation or type 2 diabetes mellitus(FPG≥5.6mmol/L and/or a two hour glucose value≥7.8mmol/L) .Patients with a HbA1c＞7.5% will be excluded from the study.  4.Course of diabetic mellitus less than 1 year |

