**Safty and monitoring board**

An independent Ethics Committee of Zhongshan Hospital (ECZH) ,Fudan University approved the protocol for the trial and is responsible for monitoring the accumulated interim data as the trial progresses to ensure patient safety and to review efficacy. In addition, the committee is charged with reviewing the quality and timeliness of data collection. Interim data on safety measures requested by the ECZH are reviewed at each of the scheduled semi-annual meetings. Serious adverse events are reviewed by the ECZH as they occur and the ECZH reviews quarterly reports about the count of patients who present hepatic or renal toxicities during the study. One interim efficacy analysis of the primary outcome measure is planned to occur when approximately 50% of the data are complete or when approximately 90 of the 180 patients have completed baseline and 16 week MRS examination. O'Brien-Fleming statistical stopping guidelines for efficacy apply

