**4.3 Outcomes**

The primary outcomes are the changes in OGTT (glucose, insulin, AUC of glucose), HbA1c; lipid profile（TC, TG, HDL-c, LDL-c, ApoA, ApoB, ApoE, Lpa); liver enzymes (ALT, AST, γ-GT, ALP). The secondary outcome is liver fat content by 1H NMR spectroscopy.

Safety endpoint includes serious adverse events and non-serous adverse events. Adverse event collection was conducted at each visit after baseline. No specific laboratory safety tests are required during this study. However, if a laboratory abnormality is clinically relevant or leads to an adverse event report, specific appropriate actions may be required. ECG will be performed at the beginning and end of the study.

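### The sample size and 90% power rest on liver fat, which the protocol makes secondary; none of the 16 named primary measures has a power basis

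*Protocol*

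**What the plan says.** Section 10.2 fixes 180 patients, 60 per group. It describes the basis as follows: "The sample size estimates were based upon a two-group, binomial comparison of the proportions of patients satisfying the decrease in liver fat content". The spread entered in the formula is that of liver fat itself: "with a standard deviation of NAFLD patients liver fat content (s=6.87%, from our prior study". The target δ = 0.05 is worded there as a between-group gap in the share of patients who improve. Alpha is set at 0.016, two-sided, and power at 90%. The section refers to pioglitazone versus control and berberine versus control as the two primary comparisons.

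The outcome sections say something else. Section 4.3 names as primary the changes in OGTT glucose, insulin and glucose AUC, HbA1c, eight lipid measures and four liver enzymes: 3 + 1 + 8 + 4 = 16 measures. It then adds: "The secondary outcome is liver fat content by 1H NMR spectroscopy". The synopsis and sections 1.1 and 4.1 give the same ranking. Section 3.1 builds the primary objective on the same 16 measures, and section 3.2 lists change in hepatic fat among the secondary outcomes.

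Two other places lean back towards liver fat. The synopsis states its primary objective as the effects and safety of the two drugs "on hepatic fat content and glucose and lipid metabolism in NAFLD patients", with liver fat first. The safety and monitoring board text plans one interim efficacy analysis of the primary outcome measure, in the singular, to take place at about half of the data or when "approximately 90 of the 180 patients have completed baseline and 16 week MRS examination". O'Brien-Fleming guidelines apply to that analysis.

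**The concern.** A power statement belongs to the endpoint whose SD and target difference went into it. Here that endpoint is ranked secondary, and the endpoints ranked primary have no such inputs anywhere in the protocol. A reader who sees 180 patients and 90% power beside a list of glucose, lipid and enzyme outcomes will credit those outcomes with a power that was never calculated for them.

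Three things are at stake. A null result on a named primary could not be told apart from low power. A clear liver fat result, the one the trial was sized to find, would formally be only secondary. The interim stopping rule has no unambiguous target either: it is said to act on the primary outcome, but is timed by completed MRS examinations.

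This is not a detail left to the SAP. The protocol itself fixes the sample size, its basis and the outcome ranking, and they disagree.

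**Working it through.** **1. Reproduce the stated sample size.** Inputs from section 10.2: s = 6.87, δ = 5 (the printed 0.05 read as percentage points of liver fat), two-sided alpha 0.016, power 90%. Normal quantiles: 2.41 for alpha 0.016 and 1.28 for 90% power.

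n per group = 2 × [(2.41 + 1.28) × 6.87 / 5]² = 51.4, rounded up to 52. This is the protocol's figure.

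Inflation: 52 × 1.15 = 59.8, so 60 per group and 180 in total. This also agrees.

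The liver fat inputs alone therefore yield 52, 60 and 180. Reading δ as 5 points is an inference from this match, because section 10.2 words δ as a difference in proportions improved.

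**2. Look for the same inputs on the named primaries.** None of the 16 measures has an SD, a target difference or a power figure in section 10.2 or elsewhere. A corrected sample size for them cannot be computed from the protocol.

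**3. What the fixed sample size would detect on a named primary.** Evaluable patients per arm: 60 × 0.85 = 51. Section 10.3 uses a threshold of 0.025 per comparison (quantile 2.241). For one measure taken alone, in an unadjusted two-group comparison:

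detectable difference = (2.241 + 1.282) × √(2/51) = 3.523 × 0.198 = 0.70 SD.

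At section 10.2's own alpha of 0.016 it is 0.73 SD. For comparison, the planned liver fat effect is 5 / 6.87 = 0.73 SD.

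**4. Allow for the planned analysis.** Section 10.3 specifies ANCOVA adjusting for the baseline value. If r is the correlation between baseline and week 16, the detectable difference is about 0.70 × √(1 − r²) in units of the week-16 SD. The protocol gives no r, so these values are assumptions:

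| Assumed r | Detectable difference (week-16 SD) |
|---|---|
| 0.3 | 0.67 |
| 0.5 | 0.60 |
| 0.7 | 0.50 |

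**5. Power if the true effect is smaller.** Unadjusted, 51 per arm, two-sided 0.025, normal approximation. The standardised effects are assumed, since the protocol offers none:

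| Assumed effect (SD) | Power |
|---|---|
| 0.3 | 23% |
| 0.4 | 41% |
| 0.5 | 61% |
| 0.6 | 78% |
| 0.7 | 90% |

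The 90% carries over to a primary measure only if its standardised effect is about as large as the one planned for liver fat, or if baseline adjustment makes up the gap.

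**The case against.** The mismatch itself has no good defence, but there are fair objections to pressing it further.

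*The trial is underpowered for its primaries.* A reader might infer this. The protocol does not show it: with no SD, effect or correlation for any of the 16 measures, their power is unknown, not known to be low. Baseline adjustment could bring the detectable difference well under 0.70 SD. This objection stands, so 0.70 may be quoted only as an unadjusted figure.

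*The design delivers its power for liver fat, about 92% at 0.025.* That goes too far. It depends on reading δ as 5 points, whereas the text speaks of a binomial comparison of proportions. At section 10.2's own 0.016, 51 per arm give about 89.7%. The SD is described as that of liver fat content, not of its 16-week change. Section 10.2 also says that no berberine steatosis data were available and that the pioglitazone response was assumed. What can be said is that 52 reproduces under those inputs.

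*Entry limits leave the named primaries little room to improve, and only liver fat has an entry floor.* The caps on HbA1c, ALT/AST and triglycerides are real, but inclusion criterion 3 also sets a floor on glucose (fasting and/or 2-hour), and OGTT glucose is a named primary. The room left is not quantified. The point does not need this argument.

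*Liver fat is plainly the intended primary.* The synopsis objective, the interim timing and the sizing point that way; the explicit outcome statements point the other way. The documents conflict and do not settle it.

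**Conclusion.** The point holds as a contradiction within the protocol. The 52 per group, the 180 in total and the 90% power come from liver fat inputs alone. Liver fat is ranked secondary in the synopsis and in sections 1.1, 3.2, 4.1 and 4.3, and the 16 named primaries have no power basis. As written, the 90% cannot be claimed for any of them, and it is unclear which endpoint the O'Brien-Fleming rule governs.

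The size can be given only as a detectable difference: about 0.70 SD per measure at two-sided 0.025 with 51 evaluable per arm, unadjusted, and roughly 0.67 to 0.50 of the week-16 SD under ANCOVA for assumed r of 0.3 to 0.7. These figures assume the 15% loss in section 10.2, a normal approximation and no correction across the 16 measures. The protocol nowhere states that effects of this size are expected. This should be corrected before the trial's conclusions rest on it.

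**What to change.** Make the outcome ranking and the sample-size basis agree, in one of two ways.

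(a) Name the 16-week change in MRS liver fat as the single primary endpoint in the synopsis, sections 1.1, 3.1, 3.2, 4.1 and 4.3, and the interim analysis text. Move the glucose, lipid and enzyme measures to secondary. Describe section 10.2 as a comparison of means, with δ in percentage points of liver fat. Section 3.2 must be edited too, or liver fat would be both primary and secondary.

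(b) Keep the present primaries. State in section 10.2 that the 90% power applies only to the secondary liver fat outcome, and give the detectable standardised difference for the primaries with its assumptions: 0.70 SD at 0.025 unadjusted, smaller under ANCOVA depending on r. Say in the interim text which outcome the stopping rule acts on.

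Neither option adds patients or procedures, because the schedule already has MRS at V0, V1 and V5. Option (b) is a change of wording. Option (a) is comparably cheap only if made before any outcome data are seen: the trial is open-label with an interim efficacy look, so a later change of primary endpoint would be open to the charge of being data-driven. The protocol mixes past and future tense, so its text does not show how far the trial had progressed.

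### Section 10.2 describes a 0.05 difference in the proportion improved, but its 52 per group and 90% power belong to a 5 percentage-point difference in mean liver fat

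*Protocol*

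**What the plan says.** Protocol section 10.2 gives two descriptions of one calculation.

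The first is binary. The basis is a "two-group, binomial comparison of the proportions of patients satisfying the decrease in liver fat content". The expected proportions improved are said to come from pilot pioglitazone studies, and berberine is assumed to do as well. The effect size enters as "with an expected difference in proportion of improvement between pioglitazone or berberine group and the control group (δ=0.05").

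The second is continuous. The method is given in one line: "The sample size calculations were performed using the formula: n1=n2=2[(tα+ t2β)s/δ]^2". What goes into it as the measure of spread is the "standard deviation of NAFLD patients liver fat content (s=6.87%, from our prior study"). The error rates are a two-sided α of 0.016, adjusted for having three groups, and 90% power. The result is 52 per group, raised to about 60 for 15% missing data, or 180 in all.

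No response proportion is given for any arm. Section 10.3 compares changes from baseline to 16 weeks by analysis of covariance adjusted for baseline and lists no comparison of responder proportions. The synopsis (Primary Statistical Analysis) does use binary language: a patient without the required data counts as unimproved on the primary outcome measure. Section 10.3 instead leaves missing values missing.

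**The concern.** A binomial calculation needs two response proportions and has no use for the SD of a continuous measurement. A means calculation needs a difference and an SD in the same units and has no use for response proportions. Section 10.2 describes the first and carries out the second, so the label on δ does not fit the formula that δ is put into.

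A sample size statement tells an ethics committee or reader which effect the trial can detect. As worded, this one claims 90% power to detect 5 more improved patients per 100. The effect behind the patient number, a 5-point absolute difference in mean liver fat, has to be worked out backwards, so nobody is invited to ask whether it is plausible or clinically relevant. The test named as the basis for the patient number is also not among the analyses in section 10.3.

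**Working it through.** **Inputs, all from section 10.2:** s = 6.87% (liver fat content); δ = 0.05; α = 0.016 two-sided; power 90%; stated result 52 per group.

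**Step 1. Reproduce the stated figure.** Take δ as 5 percentage points of liver fat, the same scale as s (0.05 against 0.0687).

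- z(1 − 0.016/2) = 2.409; z(0.90) = 1.282; sum 3.690
- n = 2[(zα + zβ)s/δ]² = 2[3.690 × 6.87/5]² = 51.4, so **52 per group**
- Power at 52 per group: 90.4%
- With t quantiles in place of normal ones the formula gives 52.8, and the exact noncentral t gives 53

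The stated 52 is therefore a comparison of means with δ = 5 points.

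**Step 2. Take the description at its word.** Compare p and p + 0.05 at two-sided 0.016 with 90% power. The protocol gives no control rate, so a range is assumed. With d = 0.05 and p̄ the mean of p₁ and p₂:

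- n = [zα√(2p̄(1 − p̄)) + zβ√(p₁(1 − p₁) + p₂(1 − p₂))]² / d²
- Power at n per group = Φ{[d√n − zα√(2p̄(1 − p̄))] / √(p₁(1 − p₁) + p₂(1 − p₂))}

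Example, 0.30 against 0.35: the two square roots are 0.6624 and 0.6614.

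- n = (2.409 × 0.6624 + 1.282 × 0.6614)² / 0.0025 = 2,388
- Power at 52 = Φ[(0.3606 − 1.5956)/0.6614] = Φ(−1.87) = 3.1%

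| Assumed control rate | n per group for 90% power | Power at 52 per group | Power at 60 per group |
|---|---|---|---|
| 0.05 | 754 | 7.4% | 8.5% |
| 0.10 | 1,190 | 5.0% | 5.6% |
| 0.20 | 1,898 | 3.6% | 4.0% |
| 0.30 | 2,388 | 3.1% | 3.4% |
| 0.40 | 2,661 | 2.9% | 3.2% |
| 0.475 (largest n) | 2,722 | 2.9% | 3.1% |
| 0.50 | 2,715 | 2.9% | 3.1% |
| 0.60 | 2,552 | 3.0% | 3.3% |

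The unpooled variance gives nearly the same: 749 per group and 7.6% power at a control rate of 0.05. Even at an assumed control rate of 0.01, 366 per group would be needed and 52 would give 15% power. With 52 per group, 90% power on a binary outcome needs a difference of about 31 to 36 points for control rates of 0.10 to 0.50.

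**Step 3. What the SD refers to.** Section 10.2 gives 6.87% as the SD of liver fat content, not of the 16-week change. If the baseline and 16-week SDs are equal with correlation ρ, the SD of change is 6.87√(2(1 − ρ)), and n for a simple comparison of changes is 51.4 × 2(1 − ρ):

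- ρ = 0.3: SD 8.13, about 72 per group
- ρ = 0.5: SD 6.87, 52 per group
- ρ = 0.7: SD 5.32, about 31 per group

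Applying 6.87 to the change therefore assumes ρ of about 0.5. Baseline-adjusted analysis of covariance would give a different n again.

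**The case against.** The strongest reply is that nothing numerical is wrong. Formula, SD, α, power and 52 agree with each other, and the planned analysis is also of continuous changes. Liver fat content is itself a percentage, and the SD stands in the same sentence as δ, so a statistician will see that 0.05 and 6.87% share a scale and recover the intended effect. On this view the defect is one mislabelled symbol, and the figures of 750 to 2,720 per group describe a calculation that the sponsor did not run. Much of this stands. The arithmetic is sound, and the effect can be recovered by working back from the 52.

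It does not dispose of the point, because the binary description is more than one word. Section 10.2 gives it three times, in the basis of the estimate, the expected proportions and the definition of δ. The synopsis also has an improved/unimproved rule. A reader cannot tell from the text whether a responder comparison was intended.

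Two stronger readings are tempting and are not supported. One is that 52 is a miscalculation, or that the trial has only 3% to 8% power. Those figures apply to the effect as labelled and say nothing against 90% power for a 5-point difference in mean liver fat. The other is that the lack of a responder definition is itself an error. That may be left to the statistical analysis plan, which is not at hand. The point here is a contradiction within the protocol.

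**Conclusion.** The point holds as a misdescription of the effect and test, not as an arithmetic error. The 52 per group and the 90% power are right for a two-sample comparison of means with δ = 5 percentage points of liver fat, SD 6.87 points and two-sided α 0.016. They do not hold for a 0.05 difference in the proportion improved, where power at 52 per group is about 3% to 8%. That range rests on assumed control rates of 5% to 60%, but no rate in it brings power anywhere near 90%.

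The correction is worth making because the protocol attaches its power claim to the wrong effect. One caution limits how it is worded: 52 per group carries over unchanged only while 6.87 remains the SD of liver fat content. A rewrite in terms of 16-week change would bring in a correlation assumption that the protocol does not state.

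**What to change.** 1. In section 10.2, restate δ as an absolute difference of 5 percentage points in mean liver fat content between each drug and control, tested by a two-sample comparison of means, with 6.87 percentage points described as the SD of liver fat content. If the SD is meant to apply to the 16-week change, say so and justify the implied baseline to week-16 correlation of about 0.5.
2. Delete the binomial and proportion-improved wording from section 10.2.
3. Reconcile the synopsis rule that treats patients without data as unimproved with section 10.3, which analyses continuous changes by analysis of covariance and leaves missing values missing. Editing 10.2 alone would leave that rule with no analysis to attach to.
4. If a responder comparison is truly intended, state both proportions and restate the power that 52 to 60 per group gives.

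Items 1 to 3 are wording changes. They leave 52 per group and the total of 180 as they are, provided the SD stays that of liver fat content or the correlation is justified. Item 4 would replace the 90% power claim.

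This change does not settle two separate matters: liver fat is a secondary outcome in section 4.3, and α is 0.016 in section 10.2 but 0.025 in section 10.3.
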